## Abstract

**Background:**

Potent combined antiretroviral therapy decreased the incidence and severity of HIV-associated neurocognitive disorders (HAND); however, no specific effective pharmacotherapy exists for HAND. Patients with HIV commonly have deficits in working memory and attention, which may negatively impact many other cognitive domains, leading to HAND. Since HAND may lead to loss of independence in activities of daily living and negative emotional well-being, and incur a high economic burden, effective treatments for HAND are urgently needed. This study aims to determine whether adaptive working memory training might improve cognitive functions and neural network efficiency and possibly decrease neuroinflammation. This study also aims to assess whether subjects with the *LMX1A*-rs4657412 TT(AA) genotype show greater training effects from working memory training than TC(AG) or CC(GG)-carriers.

**Methods/Design:**

60 HIV-infected and 60 seronegative control participants will be randomized to a double-blind active-controlled study, using adaptive versus non-adaptive Cogmed Working Memory Training® (CWMT), 20–25 sessions over 5–8 weeks. Each subject will be assessed with near- and far-transfer cognitive tasks, self-reported mood and executive function questionnaires, and blood-oxygenation level-dependent functional MRI during working memory (*n*-back) and visual attention (ball tracking) tasks, at baseline, 1-month, and 6-months after CWMT. Furthermore, genotyping for *LMX1A-*rs4657412 will be performed to identify whether subjects with the TT(AA)-genotype show greater gain or neural efficiency after CWMT than those with other genotypes. Lastly, cerebrospinal fluid will be obtained before and after CWMT to explore changes in levels of inflammatory proteins (cytokines and chemokines) and monoamines.

**Discussion:**

Improving working memory in HIV patients, using CWMT, might slow the progression or delay the onset of HAND. Observation of decreased brain activation or normalized neural networks, using fMRI, after CWMT would lead to a better understanding of how neural networks are modulated by CWMT. Moreover, validating the greater training gain in subjects with the *LMX1A*-TT(AA) genotype could lead to a personalized approach for future working memory training studies. Demonstrating and understanding the neural correlates of the efficacy of CWMT in HIV patients could lead to a safe adjunctive therapy for HAND, and possibly other brain disorders.

**Trial registration:**

ClinicalTrial.gov, NCT02602418.

## Background

The incidence of HIV-associated dementia has declined dramatically since the introduction of potent combined antiretroviral therapy; however, milder forms of HIV-associated neurocognitive disorders (HAND) persist. Some 30 to 50 % of HIV-infected individuals have HAND, which is more prevalent in those older than 50 years [1, 2]. Other co-morbidities, such as substance abuse (e.g., alcohol, cannabis, or psychostimulants) and hepatitis C infection, further exacerbate or hasten the development of HAND, partly owing to poorer medication adherence compared with those without HAND [3, 4]. With an increasing proportion of HIV-infected individuals at risk of HAND, which leads to both functional and occupational disabilities, the development of effective treatments or adjunctive therapy for these patients is critical.

The current therapy for HIV infection leaves a ‘therapeutic gap’ for HAND [1, 2]. Combined antiretroviral therapy is effective at suppressing the viral burden but cannot reverse HAND completely or prevent the development of HAND, even in those with long-standing aviremia [5]. In addition, antiretroviral drugs may have adverse or neurotoxic effects on the brain [6–8]. A number of pharmacological trials, including trials of minocycline [9], CEP-1347 [10], memantine [11], lithium [12], peptide T [13], and selegiline [14–16], were conducted with no clear efficacy for cognitive improvements, although some of these studies demonstrated positive effects on neuroimaging measures in human beings or immunohistochemistry in animal models. Therefore, no evidence-based treatment is available to improve the cognitive function of patients with HAND. In addition, neuropathological, neuroimaging, and cerebrospinal fluid studies consistently showed ongoing aberrant neuroinflammation, with persistent glial activation [17], and lesser dopamine transporters [18, 19]; both may contribute to brain injury and HAND in HIV patients. Hence, effective treatment for HAND might require a multimodal approach.

Another important reason to develop an effective treatment is that HAND leads to higher healthcare costs. For instance, a study of patients with HIV or AIDS in a community-based clinic in Canada found that the care for those with a neuropsychiatric disorder was more costly, both immediately before and after the diagnosis, regardless of the specific neuropsychiatric diagnosis [20]. Likewise, an Australian study showed that with the predicted doubling of HIV infection in men and tripling in women over the next two decades, the cost of care could nearly double at the current 7 % prevalence of HIV-associated dementia, primarily for residential care [21]. Another study from Sweden on the pharmacoeconomics of mild cognitive impairment showed that postponing the development of dementia even for a few years after diagnosis of mild cognitive impairment would result in cost savings of approximately $5,300 per person [22]. Therefore, an effective treatment for HAND or to delay the onset of HAND, even in a subset of HIV-infected individuals, might lead to significant cost savings.

The major cognitive domains affected in HAND are attention and working memory [23, 24], in both visual and verbal domains [25–28]. Working memory is defined as the cognitive skill to retain and manipulate information ‘online’ over short periods of time. Working memory is thus necessary for concentration and maintaining awareness and is crucial for learning and executive functions, such as reasoning and planning. Working memory is also needed in daily life in all settings. Hence, deficits in working memory may negatively affect many other cognitive domains. While the introduction of combined antiretroviral therapy led to generally improved neuropsychological function, working memory dysfunction was not improved or was even exacerbated with ongoing infection [1, 29]. Working memory dysfunction in HIV has major consequences, such as being a strong predictor of unemployment and dependence in activities of daily living [30], self-reported cognitive complaints [31], and poorer medication adherence [32, 33]. Therefore, enhancing working memory ability and delaying progression of working memory decline should benefit HIV-infected individuals.

Importantly, working memory skills can be trained, for instance, using Cogmed Working Memory Training® (CWMT), a computer-based adaptive working memory training program that is effective for improving cognition. The efficacy of CWMT was first demonstrated in children with attention deficit hyperactivity disorders [34], who showed better non-verbal and verbal working memory performance and improved response inhibition and reasoning, as well as reduced parent-rated inattentive symptoms of attention deficit hyperactivity disorders [35]. Patients with traumatic brain injury also had improved functioning in daily life activities, which was maintained even 6 months after CWMT [36]. Other populations who benefitted from CWMT included stroke victims [37], adolescents born preterm with extremely low birth weight [38], children with cochlear implants [39], and healthy older persons [40]. However, this remarkably safe and innovative intervention has not been evaluated as an adjunctive therapy for HAND.

To our knowledge, no study has investigated the neural correlates of working memory training in HIV patients, or whether neural networks might re-organize or show corresponding improved neural efficiency. Working memory deficits in HIV patients probably involve injuries to the frontostriatal circuits, which are brain regions that have been shown in neuropathological studies [41] to be preferentially affected in HIV patients. Working memory deficits have been observed in encoding [23], reaction times [42], and simultaneous short-term storage and processing [43], suggesting subcortical deficits as well as abnormalities of the prefrontal cortex [26]. The brain is highly ‘plastic’ in that brain activities and network connections can change quickly and that changes can last for a long time after a task is practiced, as found in tasks involving visual attention [44], object naming [45], motor learning [46, 47], and working memory [48–50]. Blood-oxygenation level-dependent functional magnetic resonance imaging (BOLD-fMRI) studies following 5-weeks of adaptive CWMT showed increased training-related activity in the medial frontal gyrus and parietal cortices for the trained tasks [51, 52] and in the the inferior frontal gyrus for the untrained tasks with varied working memory load [52]. However, compared with fixed low-level training (active control condition), older adults who received adaptive working memory training showed decreased brain activation in frontal, parietal, and temporal cortices but increased activity in the caudate and thalamus [53]. Transfer of performance improvement (gain) to untrained tasks (transfer of gain) requires overlapping networks and brain regions common to both tasks, especially the striatum [54]. Our proposed fMRI studies will further assess brain changes associated with improvements on working memory and other cognitive tasks.

Recent data also indicate that individuals with different genotypes for dopamine-related genes may have different training gain, such as polymorphisms in *LMX1A* [55] and *catechol-O-methyltransferase Val158Met* [56]. This study will focus on *LMX1A*, which encodes for the protein LIM homeobox transcription factor 1 alpha, a positive regulator of insulin gene transcription, but is also involved in the proliferation, differentiation, and maintenance of dopamine-producing neurons in the midbrain [57–59]. Polymorphisms in *LMX1A* were associated with dopaminergic disorders, such as Parkinson’s disease [60] and schizophrenia [61], and, recently, with the effects of working memory training [55]. Specifically, subjects with TT(AA) alleles at the *LMX1A*-rs4657412 had greater training-related gains in verbal working memory than those with heterozygous TC(AG) or CC(GG) alleles [55]. Since HIV patients commonly showed dopaminergic deficits, with decreased dopamine transporters [18, 19] and decreased cerebrospinal fluid dopamine and dopamine metabolites [62], we will explore whether genetic variations of *LMX1A*-rs4657412 modulates working memory training effects and cerebrospinal fluid monoamines and their metabolites in our subjects.

Based on this prior knowledge, the current study has three major aims and one exploratory aim.Aim 1: To perform a double-blind active-controlled study on the effectiveness of CWMT (25 sessions over 5–8 weeks) in HIV-infected and seronegative subjects, with or without cognitive deficits, and assess whether the training will improve cognitive functioning (on working memory and some non-trained tasks that require working memory) at 1 month (to assess gain) and 6 months (to assess maintenance of gain) after the training.Aim 2: To assess the neural correlates of working memory training, and determine whether brain activation will improve, at 1 month and 6 -months after the training, as assessed by functional MRI (fMRI) during working memory and attention tasks.Aim 3: Since individuals with the TT(AA) genotype for the single nucleotide polymorphism *LMX1A*-rs4657412 had greater magnitude of training-related gains in verbal working memory [55], we will assess our subjects for the allelic variations on training results (gain and maintenance).

### Exploratory aim

We will explore changes in neuroinflammatory markers, and monoamine and their metabolites in the cerebrospinal fluid before and at least 1 month after CWMT, and evaluate the relationships between cerebrospinal fluid markers, cognitive performance, and BOLD-fMRI signals.

## Methods/design

The proposed study uses a 2 × 2 repeated-measures analysis of covariance (ANCOVA) design to evaluate the effects of 5 weeks of CWMT, adaptive versus ‘active control (fixed low level)’ training, as assessed by the improvement index (generated from task performances within the CWMT), neurocognitive testing, BOLD-fMRI measurements, cerebrospinal fluid neuroinflammatory proteins, monoamine, and metabolite levels. We propose to enroll 60 HIV-infected individuals and 60 seronegative healthy participants, with 30 adaptive and 30 active-control-training subjects randomized in each group (Fig. 1). HIV-positive and seronegative subject groups will be matched by age, sex, education, socioeconomic status, and cognitive status (matched by global cognitive score from the seven cognitive domains tested), as well as other co-variates (e.g., nicotine smoking and other substances abused). Based on the initial screening evaluations, subjects who fulfill all study criteria will be scheduled for a baseline neuropsychological evaluation, MRI-fMRI scans, and a lumbar puncture.

**Fig. 1 Fig1:**
[figure not shown]
Study design. We plan to screen ≈ 500 individuals initially by telephone and 200 of these potentially eligible participants in person, to identify ≈ 150 subjects who will fulfill our study criteria, and complete the baseline evaluation. We expect that only ≈ 120 (60 HIV and 60 seronegative) will follow through and be randomized for the training. We also expect that only 85 % (*n* = 102, 50 HIV, and 52 seronegative) will return for the 1 month follow-up and only 80 % of these (*n* = 86, 40 HIV, and 42 seronegative) will return to complete the 6-month follow-up evaluations. Furthermore, we expect that ≈ 20 participants who completed the ‘active control’ training will want to continue with the ‘adaptive training’. CSF, cerebrospinal fluid; I/E, inclusion or exclusion; MR, magnetic resonance; SN, seronegative; WM, working memory.

### Primary and secondary outcome measures

The main goal of this study is to examine the effectiveness of intensive adaptive working memory training for the treatment of HAND. The primary outcome measures will be the improvement index on CWMT, improvement on non-trained near-transfer working memory tasks, and changes on brain activation assessed with BOLD-fMRI during working memory and attention tasks. Secondary contrasts will evaluate genotype effects (*LMX1A*, TT(AA) versus TC(AG) or CC(GG)) on cognitive improvements and BOLD-fMRI. We will also assess CWMT-related improvements on self-reported depressive and various psychopathological symptoms, using the Center for Epidemiological Studies–Depression Scale Revised and Symptom Checklist–90 revised items, and on self-rated functionality, using the Independent Activity of Daily Living assessment and the Behavior Rating Inventory of Executive Function–Adult Version.

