Mental control	✓	✓	✓General intelligence: the Wechsler Test of Adult Reading will provide an estimate of premorbid intellectual functioning during our screening procedure to ensure that the subjects have a verbal intelligence quotient > 80 and can provide consent. The Wechsler Adult Intelligence Scale IV will be used to evaluate general cognitive ability (intelligence quotient) for all subjects at baseline.Assessments of changes in working memory, other cognition and function (primary outcomes) will be administered repeatedly at baseline, 1 month after training (either adaptive working memory or ‘active control’ training condition), and 6 months after the adaptive working memory training. Alternative word lists or stories will be used for repeated testing. Table 2 shows the tests involved in the trained working memory tests, which will include the ‘start index, maximum index, and improvement index’, the non-trained working memory tests and the transfer of working memory capacity gain to other cognitive functions.

For the non-trained working memory tasks, no practice effects are expected [64]. However, for the other neuropsychological tests, variable degrees of practice effects will occur with test–retest [65]; we will control for such practice effects by performing the same tests before and after CWMT in both HIV-positive and seronegative control subjects.

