### Cognitive intervention using Cogmed® RM

The Cogmed® RM (Table 3) was developed for school-aged children; however, we chose this version for our adult participants since it is more colorful and appealing to the participants than the adult version (Cogmed® QM). The training program consists of 25 training sessions (minimum of 20 required), 30–40 minutes per day, 4–5 days per week over a 5–8 week period [35]. Subjects will perform either the ‘active control’, with a fixed low level across each task, or an ‘adaptive’ version, with increasing difficulty for the working memory tasks. The training will be performed either in the participants’ homes, or at the research laboratory. We will ensure that participants have high-speed internet access. Subjects will be trained using verbal and non-verbal working memory tasks that involve: (1) maintenance of several stimuli at the same time; (2) short delays during which the representation of stimuli should be held in the working memory; (3) unique sequencing of stimulus order in each trial. Training will be supplemented with weekly guidance by trained ‘coaches’, who can review subjects’ progress online and will telephone them to give feedback, motivation, and advice to optimize their training experience.

**Table 3 Tab3:** Description of the 12 modules in Cogmed® Working Memory Training

Task	Description
Verbal working memory (with visuospatial components)	
Input module (numbers)	A panel with 1 to 9 is shown. Numbers are presented aurally and light up on the panel sequentially. Participants then have to click on the numbers in the reversed sequence.
Input module with lid (hidden numbers)	Same as previous task, except numbers are presented aurally only, since they are covered by a lid, which opens when all the numbers are read.
Stabilizer (letters)	A circle of lamps is shown. A sequence of letters is presented aurally along with specific lamps that light up. Participants are then presented with a letter in the middle of the circle, and have to click on the lamp that lit up.
Decoder	Letters are read sequentially along with a lamp that lights up. The participant then has to reproduce the sequence by selecting one letter from three possible letters below each lamp.
Visuospatial working memory	
Visual data link (grid)	Lamps light up sequentially in a 4 × 4 grid, and the participant must reproduce the sequence by clicking on the lamps in the same order afterwards.

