### Statistical analysis

All analyses will be performed using SAS, using repeated-measures analysis of variance (ANOVA) as the primary model (co-varied for age and sex). The baseline (initial) values of all key variables will be tested for normality prior to analysis. Appropriate transformations (or non-parametric tests) will be used as necessary. The statistical significance will be determined using a modified Bonferroni procedure for multiple tests [71]. The procedure will have a type I error probability equal to 0.05 for independent tests.

Neurocognitive assessments will be tested using appropriately constructed contrasts within a 2 × 2 repeated-measures ANOVA model. HIV status (and HAND status for subgroup analyses) and training condition (adaptive versus fixed) will be across-subjects variables, and time (baseline, 1-month, 6-months) will be within-subject variables. Analyses will be co-varied for subject age, sex, and other co-variates as needed (e.g., depression scores). Subjects trained in both the adaptive and fixed training will have the training condition as a within-subject variable.

The fMRI time series will be analyzed using Statistical Parametric Mapping software (SPM8, Welcome Department of Cognitive Neurology, UK). After spatial normalization and smoothing, maps of brain activation and differential changes in activation (repeat − baseline) will be calculated for each subject and task, using a fixed-effects model with a block design. In a subsequent random-effects analysis, differences between groups on BOLD signal changes will be evaluated for each task (*t* tests or ANOVA). Statistical significance will be based on cluster-level significance at *P* < 0.05 corrected for multiple comparisons (voxel-level threshold *P* < 0.05, cluster size >100 voxels). Additionally, we will extract regional percentage BOLD-fMRI signals from cubic regions of interest (0.729 cm^3^) centered at cluster maxima, using a customized program written in Matlab. The extracted data will be imported into SAS, where a repeated-measures ANOVA model will be run to confirm and further evaluate the statistical parametric mapping findings.

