## Dissemination plan

At the completion of this trial, we plan to submit several manuscripts to peer-reviewed journals including;‘Neural correlates of adaptive working memory training in HIV patients’: this paper will report on the interim findings from the primary outcome measures, including improvements on working memory performance and neural efficiencies, 1 month and 6 months after the adaptive version of CWMT, to assess the gain and maintenance of working memory improvements after training. Some of the secondary contrast results, including scoring on the Behavior Rating Inventory of Executive Function–Adult Version and *LMX1A* genotype effects, will also be reported. These findings may lead to a larger study to validate whether CWMT can be used as an adjunctive therapy for HAND.‘Computerized working memory training in HIV patients: a double-blind active control study’: this paper will be written at the completion of subject enrollments. We will compare the effects of adaptive versus fixed low level of CWMT on the primary outcome measures, at 1 month and 6 months after training compared with baseline assessments. This will provide further evidence of whether CWMT is effective for working memory and attention deficits in HIV patients.This paper will also report on the findings after the double-blind active control study to evaluate the efficacy of CWMT on the secondary outcome measures, including scores on the the Center for Epidemiological Studies–Depression Scale, Revised, and the Symptom Checklist–90–revised, and ability to conduct activities of daily living (Independent Activity of Daily Living assessment and the Behavior Rating Inventory of Executive Function–Adult Version) before and after CWMT.This paper will report on possible improvements in cerebrospinal fluid neuroinflammatory proteins (chemokines and cytokines) and neurochemicals (dopamine and serotonergic levels and their metabolites) after CWMT. Since only half of the participants might consent to the lumbar punctures, we may need to combine results from the adaptive training group and the fix-low-level training group to evaluate the training effects on these cerebrospinal fluid measurements.

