### Expected findings

#### Gain in working memory performance and transfer of gain to ‘near’ or ‘far’ transfer tasks (Aim 1)

HIV-positive subjects commonly have working memory deficits [3, 23–29, 41–43]. Since working memory is needed to maintain focus on tasks, deficits in working memory may negatively affect many other cognitive domains, and result in HAND. Prior studies of CWMT showed that the program enhanced performance not only on trained working memory tasks, but also on some non-trained visuospatial and non-trained complex reasoning tasks, including executive function [73]. Therefore, we aim to evaluate the efficacy of CWMT on cognitive performance in our subjects.

We hypothesize that all subjects will show improved working memory after Cogmed® RM training (adaptive training > low fixed level ‘active control’ training), both at 1 month and at 6 months after cessation of training. In addition, not only will adaptive CWMT will lead to greater improvements than active control training on the trained tasks, but the gain will transfer to non-trained tasks that require similar working memory processes, including near-transfer tasks (e.g., digit span and spatial span) and far-transfer tasks (e.g., verbal learning, logical memory, short-term memory, and recognition memory). Lastly, we expect that the gain will be greater in subjects with normal cognition (regardless of HIV status) than in those with cognitive deficits (e.g., HAND or HAND-equivalent).

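### The CWMT improvement index is a primary outcome for adaptive versus fixed training, but controls train at a fixed low level, so the between-arm contrast is confounded with the assigned software version

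*Protocol article*

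**What the plan says.** All references are to the protocol article.

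- **Primary outcomes** (Primary and secondary outcome measures): "The primary outcome measures will be the improvement index on CWMT, improvement on non-trained near-transfer working memory tasks", followed by change in BOLD-fMRI activation.
- **Source of the index** (Methods/design): the effects of adaptive versus fixed training are evaluated "as assessed by the improvement index (generated from task performances within the CWMT", alongside measures taken outside the program.
- **Components** (Neuropsychological evaluation): the trained-task measures are named as "start index, maximum index, and improvement index". No formula or scoring rule is given.
- **The two arms** (Cognitive intervention using Cogmed RM): the active control trains "with a fixed low level across each task"; the adaptive version runs "with increasing difficulty for the working memory tasks".
- **The planned comparison** (Dissemination plan): "We will compare the effects of adaptive versus fixed low level of CWMT on the primary outcome measures".
- **The hypothesis** (Expected findings, Aim 1): "adaptive CWMT will lead to greater improvements than active control training on the trained tasks", with transfer to untrained tasks stated as a further expectation.

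**The concern.** A randomised comparison needs an outcome on which both arms can score in the same way. Here the instrument is the intervention. One version of the software offers harder items as the participant progresses and the other never does. A control participant whose working memory grew could not show it on an index of level reached, because no harder level is presented.

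The stated goal is effectiveness for treating HAND. A difference on this index could be reported as a positive primary outcome even if nothing carried over to any test outside the program.

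**Working it through.** **Step 1. Do the sections combine as feared?**

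| Question | Answer in the article |
|---|---|
| Is the index primary? | Yes (Primary and secondary outcome measures) |
| Is it measured inside the assigned program? | Yes (Methods/design) |
| Do both arms face the same range of difficulty? | No: fixed low level versus increasing difficulty (Cognitive intervention) |
| Are the arms compared on it? | Yes (Methods/design, Dissemination plan, Expected findings Aim 1) |
| Is it limited to the adaptive arm, or called a process or adherence measure? | Nowhere |
| Do both arms take a common test of the trained tasks? | None described |

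The formula has to be assumed. From the three names given, a natural reading is maximum index minus start index. The argument needs less than that: any index that reflects the level reached is capped in an arm held at one low level.

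**Step 2. What the plan's own figures cover.** The Participants section gives about 17 HIV-positive subjects for an effect size of 0.7 and 26 for 0.58, at 80% power, two-sided. For a pre-post (paired) test, the normal approximation is n = ((1.960 + 0.842)/d)² = 7.85/d²:

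- d = 0.7: 7.85/0.49 = 16.02, rounded up to 17. The exact paired t calculation gives 19.
- d = 0.58: 7.85/0.3364 = 23.3, rounded up to 24. The exact paired t calculation gives 26.

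Both stated figures are reproduced to within two subjects as pre-post sizes. A two-sample calculation would give 33 and 47 per arm and does not match. So the pilot range of 0.7 to 1.2 is within-group change on four working memory tests. It is not a between-arm effect, and the article does not say that it concerns the index. The sample size does not mention the index.

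**Step 3. Illustration of size.** With no effect size for the index, the 0.7 to 1.2 range is borrowed. Assumptions:

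- The adaptive arm gains d inside the program, with SD 1.
- The control mean change is 0, with SD s.
- There is no benefit outside the program.
- The test is two-sided at 0.05, with no multiplicity adjustment.

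The chance of a significant difference is approximately Φ(d/SE − 1.96), with SE = √((1 + s²)/n).

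| n per arm | d | s = 0 (control cannot vary) | s = 1 (same SD as adaptive) |
|---|---|---|---|
| 30 | 0.7 | SE 0.183; Φ(1.87) = 97.0% | SE 0.258; Φ(0.75) = 77.4% |
| 30 | 1.2 | Φ(4.61), over 99.9% | Φ(2.69) = 99.6% |
| 60 | 0.7 | over 99.9% | SE 0.183; Φ(1.87) = 97.0% |
| 60 | 1.2 | over 99.9% | over 99.9% |

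Thirty per arm is one HIV stratum; 60 per arm pools the two. A multiplicity adjustment would lower these chances somewhat.

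**The case against.** **The formula is unseen.** An article commonly leaves scoring rules to the full protocol, so a cap on the control score is inferred, not stated. This stands, and the conclusion is conditional on it. It would fail only if the index did not depend on the level reached.

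**Trained tasks might be retested in both arms.** The Neuropsychological evaluation section mentions the trained-task indices beside assessments repeated after training, which could suggest a common retest. It points to Table 2 for them, but that table is headed as non-trained tests and lists no trained task. Methods/design says that the index comes from performance within the program.

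**A positive result is not certain.** A reader might infer that the index must come out significant even if adaptive training does nothing. The documents do not support that. A capped control arm creates no difference by itself; the adaptive arm must also rise, and by how much depends on a start index that is not described. The illustration assumes such a rise. Its null is no benefit outside the program, which differs from no improvement on the trained tasks.

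**Loss of alpha is not shown.** A reader might also infer that the index costs the other outcomes a share of alpha, say 0.05/3 = 0.0167 instead of 0.05/2 = 0.025. The plan names a modified Bonferroni procedure, of which it says "The procedure will have a type I error probability equal to 0.05 for independent tests", and does not define a family of exactly three tests. If the procedure is step-down (an assumption), rejecting one of three hypotheses leaves the next at 0.05/2 = 0.025, the same as after removal.

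**The efficacy case does not rest on the index.** Near-transfer tasks and BOLD-fMRI are measured outside the program, the sample size does not use the index, and nowhere does the article say that one positive primary outcome suffices. Within adaptive training the index is informative about HIV status, genotype and marker correlations. All of this stands. It limits the damage but does not make the between-arm contrast on the index valid.

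**Conclusion.** The concern holds for the adaptive-versus-fixed comparison on the improvement index, provided that the index reflects the level reached. That contrast is confounded with the software version and is not valid evidence of efficacy.

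The size can only be illustrated. Under the borrowed gain of 0.7 to 1.2 SD, no mean change in controls and no transfer, the chance of a significant difference is about 77% to over 99.9% with 30 per arm, and at least 97% with 60 per arm.

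The finding does not reach the near-transfer or BOLD-fMRI primary outcomes, nor the use of the index within adaptive training.

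**What to change.** 1. Remove the improvement index from the primary outcomes for adaptive versus fixed training.
2. Keep it as a training-progress measure within adaptive training: HIV-positive versus seronegative, genotype, and correlations with markers.
3. Rest the randomised cognitive comparison on the untrained near-transfer tasks, at the time points already planned.
4. Align five places: Methods/design, Primary and secondary outcome measures, Neuropsychological evaluation, Dissemination plan, and Expected findings for Aim 1. If the last two stay as they are, the between-arm claim on the trained tasks remains.

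**Cost:** wording only, with no new data or participants, since the near-transfer tasks are already collected in both arms. There is one fewer primary outcome, and the trained-task hypothesis under Aim 1 is no longer tested as a between-arm efficacy claim.
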